**11.4. Calculation of Sample Size and Rationale**

According to the results of a study by Zhou et al. (2011)3 evaluating the efficacy of US-guided HIFU for the treatment of adenomyosis, 62 people out of a total of 69 subjects experienced relief of dysmenorrhea after treatment, showing a 90% improvement success rate. Based on these results, the reference success rate was assumed as 90% in this clinical trial to calculate the number of subjects required to satisfy the hypothesis that the success rate of the ‘ALPIUS device will be non-inferior when compared to the reference success rate’.

ALPINION Medical Systems Co., Ltd. 18/45

[figure not shown]

[figure not shown]

Protocol No. APM-03 Version 1.10/Date 20180103

[figure not shown]

In addition, in the results of a recent study evaluating the efficacy of the US-guided HIFU procedure for adenomyosis, Zhang et al. (2014)5 evaluated the degree of relief of menorrhagia and dysmenorrhea and showed a success rate of 79.5% to 87.9% while Wang et al. (2009)12 suggested an improvement success rate of 66.7%; thus, we assumed that 77.7%, which is greater than the minimum value of 66.7%, would be the ‘minimum success rate that satisfies non-inferiority’ in this study (i.e. non-inferiority threshold = 77.7%-90% = -12.3%).

The statistical hypothesis of this study is as follows.

H0: PA - P0 ≤ - δ vs H1: PA - P0 > - δ

- - PA: Expected success rate of the investigational medical device
  - P0: Reference success rate
  - δ (>0): Non-inferiority threshold

To calculate the number of samples for hypothesis testing, the number of subjects satisfying the non-inferiority hypothesis was calculated as follows through PASS13 (NCSS statistics software, Kaysville, UT) based on the following assumptions: significance level of 0.025, power of 80%, reference success rate and expected success rate of this device are set at 90%, non-inferiority limit of 12.3%, the difference between the actual success rate and the reference success rate as D=0.

[figure not shown]

As a result, a total of 72 subjects were calculated, and 80 subjects were enrolled in consideration of the dropout rate of 10%.

<Reference for Calculation of Number of Subjects>

1. X Zhang et al. Effective ablation therapy of adenomyosis with ultrasound-guided high-intensity focused ultrasound. International Journal of Gynecology and Obstetrics. 2014;124:207-211.

**11.5. Observation Items, Clinical Laboratory Tests and Observation Method**

<Clinical Trial Schedule Table>

[figure not shown]

|  | Screening | Procedure day | Follow-up period | |
| --- | --- | --- | --- | --- |
| Visit day | Visit 1 | Visit 2* | Visit 3 | Visit 4 |
| Days passed | Day -30 to 0 | Day 0 | Month 1 | Month 3 |
| Visit window | - | - | ± 2 weeks | ± 2 weeks |
| Observation type | Clinic visit | Day surgery | Clinic visit | Clinic visit |
| Hospitalization |
|  |  |  |  |
| Obtain consent | √ |  |  |  |
| Inclusion/Exclusion criteria | √ |  |  |  |
| Demographic surveyl | √ |  |  |  |
| Vital signs2 | √ | √ |  |  |
| Physical examination3 | √ |  |  |  |
| Medical history survey4 | √ |  |  |  |
| ECG test5 | √ |  |  |  |
| Laboratory test6 | √ |  | √ |  |
| FSH | √ |  | √ |  |
| Pregnancy test7 | √ |  |  | √ |
| MRI8 | √ | √ | √ | √ |
| U/S9 | √ | √ | √ | √ |
| Dysmenorrhea Relief Score10 |  |  | √ | √ |
| Dysmenorrhea Score 11 | √ |  | √ | √ |
| Menorrhagia Score 12 | √ |  | √ | √ |
| SF36-v213 | √ |  | √ | √ |
| UFS-QoL (including SSS)14 | √ |  | √ | √ |
| US-guided HIFU procedure |  | √ |  |  |
| Subject satisfaction with procedure15 |  | √ |  |  |
| Adverse event/Serious |  | √ | √ | √ |
| adverse event16 |  |
| Concomitant drugs17 | √ | √ | √ | √ |

1. Demographic survey

Basic information of subjects including date of birth, sex, height and body weight

1. Vital signs

Body temperature, blood pressure (systolic/diastolic), pulse, respiration rate

ALPINION Medical Systems Co., Ltd. 20/45

[figure not shown]

[figure not shown]

Protocol No. APM-03 Version 1.10/Date 20180103

[figure not shown]

1. Physical examination

Appearance, skin, head/neck, chest/lung, heart, abdomen, urinary/genital, extremities, musculoskeletal system, nervous system, lymph nodes, other body organs

1. Medical history survey

Survey of medical history during the past 1 year

1. ECG test

Electrocardiography is performed as a screening test for the procedure. If an abnormality is found on the electrocardiogram, the subject cannot be enrolled in this clinical trial.

1. Laboratory test

Laboratory tests are performed on all subjects to evaluate their overall health, and the test items are as follows.

■ Hematology: Hemoglobin, Hematocrit, RBC count, WBC count with differential, platelet

count

■ Blood Chemistry: Alkaline phosphatase, BUN, Creatinine, SGPT(ALT), SGOT(AST), Albumin, Total protein, Total bilirubin, Uric acid, Glucose, Cholesterol, LDH, Na, K, Cl, Ca

1. Pregnancy test

For women of childbearing potential, except for subjects whose sterilization and menopause were confirmed through the questionnaire, pregnancy is confirmed using the urine HCG (however, at the Screening visit, the pregnancy test must be done within 3 days before the procedure).

1. MRI

At the Screening visit, T1- and T2-weighted images before and after contrast enhancement are taken on three orthogonal planes to check the size of the uterus, the location of the adenomyoma, the response to the contrast agent, and the beam passage. Immediately after the procedure and during the follow-up period, contrast-enhanced fat-saturated T1-weighted and T2-weighted images are acquired to check the treated volume against to the plan and to confirm the change in the size of the uterus (4 times in total).

[figure not shown]

| Model Name | Product Name | Approval No. | Importer |
| --- | --- | --- | --- |
| Ingenia 3.0T | Superconducting magnet for whole body | Import Approval No. 11-1257 | Philips Korea Ltd. |
| Magnetic resonance computerized tomography device |
|  |  |  |

1. U/S

At the screening visit, an ultrasound examination is performed to confirm the size of the uterus and the location of the adenomyoma, and during treatment, the actual treatment is monitored through the image of the ultrasound transducer built into the ALPIUS 900.Immediately after the procedure, the condition of the uterus and adenomyoma after the procedure is checked through ultrasound examination. During the follow-up period, the size of the uterus is checked by ultrasound images at Months 1 and 3. (4 times in total) Contrast agents may be used for ultrasound examination, and detailed examination methods should follow the judgment of the investigator and the standard procedures of the institution.

[figure not shown]

| Product Name | Product Name | Approval No. | Importer |
| --- | --- | --- | --- |
| LOGIQ E9 | Universal ultrasound imaging device | Import Approval No. 09-180 | GE Healthcare Korea Co., Ltd. |

ALPINION Medical Systems Co., Ltd. 21/45

[figure not shown]

[figure not shown]

Protocol No. APM-03 Version 1.10/Date 20180103

[figure not shown]

1. Dysmenorrhea Relief Score

Each subject directly evaluates the degree of dysmenorrhea relief on a 5-point scale using a questionnaire at 1 and 3 months after the procedure.

1. Dysmenorrhea Score

The symptoms of dysmenorrhea are assessed for each subject on a 5-point scale using a questionnaire before the procedure as well as 1 and 3 months after the procedure.

1. Menorrhagia Score

The symptoms of menorrhagia are assessed for each subject on a 5-point scale using a questionnaire before the procedure as well as 1 and 3 months after the procedure.

1. SF36-v2

This is a questionnaire completed directly by the subject to evaluate the overall quality of life, and consists of 36 questions in 8 domains including physical functioning, role limitation-physical, bodily pain, general health, vitality, social functioning, role limitation-emotional, mental health, and other changes in health condition, etc.

1. UFS-QoL (including SSS)

As a questionnaire completed directly by the subject to evaluate the quality of life related to the symptoms of uterine fibroids, it consists of an 8-item Symptom Severity Score and a 29-item Quality of Life questionnaire.

1. Subject satisfaction with procedure

The pain felt by the subject during the procedure and willingness to reuse depending on the satisfaction on the procedure is evaluated through a questionnaire on a 5-point scale.

1. Adverse event/Serious adverse event

Assess according to the criteria defined in Section 16 of the Protocol and record on the Adverse Event/Serious Adverse Event record form in the CRF.

1. Concomitant drugs

Drugs that may affect the results of the clinical study are prohibited, and all drugs already being taken due to underlying diseases are recorded at the time of Screening. Only the drugs added thereafter are recorded in the CRF.

- After the procedure on Visit 2, the subject can be discharged from the hospital on the day of the procedure or hospitalized for about one day according to the judgment of the investigator and the standard procedure of the hospital.

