**11.3. Inclusion and Exclusion Criteria**

**11.3.1. Inclusion Criteria**

Subjects can be enrolled in this clinical trial only if they meet all of the following inclusion criteria.

1. Adult female of at least 20 years of age
2. Pre-menopausal or peri-menopausal (FSH<40mIU/ml)
3. Adenomyosis is clinically diagnosed through MR or US imaging
4. Pain score on the Dysmenorrhea Score is at least 4 points
   - Dysmenorrhea Score

1 = Not at all (no symptoms)

2 = A little bit (slight symptoms)

3 = Somewhat (few symptoms)

4 = A great deal (considerable symptoms)

5 = A very great deal (a lot of symptoms)

1. Have not received any other treatment for adenomyosis within 3 months before HIFU procedure

*☞ In the case of hormone therapy, even within 3 months, subjects can be enrolled if five times the half-life of the drug has elapsed since the last administration.*

ALPINION Medical Systems Co., Ltd. 17/45

[figure not shown]

[figure not shown]

Protocol No. APM-03 Version 1.10/Date 20180103

[figure not shown]

1. Those who voluntarily consent to the clinical trial and are willing to comply with the protocol
2. Those who agree to use a medically accepted method of contraception for the duration of the clinical trial
   - *Medically accepted method of contraception: Physical contraceptive devices other than contraceptives through hormonal control such as condoms or installation of intrauterine contraceptive devices*

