**12.2. Assessment Criteria and Assessment Method**

<Primary Efficacy Assessment Criteria>

- Percentage Improvement in Dysmenorrhea Relief (%)
  - Definition of dysmenorrhea relief

If the degree of menstrual pain relief corresponds to Minor, Partial, or Complete on the Dysmenorrhea Relief Score

Dysmenorrhea Relief Score

- - Complete relief

② Partial relief

③ Minor relief

④ Ineffective

⑤ Exacerbated pain

- Definition of Percentage Improvement in Dysmenorrhea Relief

Proportion of subjects who met the definition of improvement in dysmenorrhea relief above at 3 months after the procedure

ALPINION Medical Systems Co., Ltd. 28/45

[figure not shown]

[figure not shown]

Protocol No. APM-03 Version 1.10/Date 20180103

[figure not shown]

<Secondary Efficacy Endpoint>

■ Percentage Improvement in Dysmenorrhea Relief (%) - 1 month after treatment

Evaluate the Percentage Improvement in Dysmenorrhea Relief (%) 1 month after the procedure using the same method as that for the primary efficacy endpoint.

■ Dysmenorrhea Score

Subjects directly evaluate dysmenorrhea symptoms on a 5-point scale as shown below before procedure and at 1 and 3 months after the procedure.

Dysmenorrhea Score

1 = Not at all (no symptoms)

2 = A little bit (slight symptoms)

3 = Somewhat (few symptoms)

4 = A great deal (considerable symptoms)

5 = A very great deal (a lot of symptoms)

■ Menorrhagia Score

Subjects directly evaluate menorrhagia symptoms on a 5-point scale as shown below before procedure and at 1 and 3 months after the procedure.

Menorrhagia Score

1 = Not at all (no symptoms)

2 = A little bit (slight symptoms)

3 = Somewhat (few symptoms)

4 = A great deal (considerable symptoms)

5 = A very great deal (a lot of symptoms)

■ Measurement of Quality of Life

Using the questionnaire filled out by the subject, the changes at 1 month and 3 months after the procedure are compared and evaluated before and after the procedure.

- SF36-v2: This is a questionnaire to evaluate the overall quality of life, and consists of 36 questions in 8 domains including physical functioning, role limitation-physical, bodily pain, general health, vitality, social functioning, role limitation-emotional, mental health, and other changes in health condition, etc.
- UFS-QOL: As a questionnaire to evaluate the quality of life related to the symptoms of uterine fibroids, it consists of an 8-item Symptom Severity Score and a 29-item Quality of Life questionnaire.

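### Menstrual pain relief is rated at calendar visits with no link to a menses, so some Month-1 ratings precede any completed post-procedure period; the Month-3 primary is little exposed

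*Protocol*

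**What the plan says.** The notes to the schedule table in Protocol Section 11.5 set the timing of the relief rating as follows: "Each subject directly evaluates the degree of dysmenorrhea relief on a 5-point scale using a questionnaire at 1 and 3 months after the procedure". The Dysmenorrhea and Menorrhagia Scores are collected before the procedure and at the same two follow-up visits. The table gives the timing tolerance as "Visit window | - | - | ± 2 weeks | ± 2 weeks", the last two entries being Month 1 and Month 3.

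Section 12.2 counts a woman as improved under this condition: "If the degree of menstrual pain relief corresponds to Minor, Partial, or Complete on the Dysmenorrhea Relief Score". The two remaining answers are ineffective and exacerbated pain. The primary endpoint is "Proportion of subjects who met the definition of improvement in dysmenorrhea relief above at 3 months after the procedure". For the secondary Month-1 rate the instruction is: "Evaluate the Percentage Improvement in Dysmenorrhea Relief (%) 1 month after the procedure using the same method as that for the primary efficacy endpoint".

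Sections 11.5, 11.6.2 and 12.2 give no recall period, do not require that a period has occurred since the procedure, and list no menstrual date. Section 11.3.1 admits women who are "Pre-menopausal or peri-menopausal (FSH<40mIU/ml") and sets no criterion on cycle regularity. For hormone therapy within the preceding three months it says that "subjects can be enrolled if five times the half-life of the drug has elapsed since the last administration".

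**The concern.** Dysmenorrhea is pain at menses, so a relief rating has content only once a menses has followed the procedure. With a calendar trigger, a woman seen early in the Month-1 window may have had no period, or may still be in her first. She then either answers about something that has not happened or leaves the item blank, and the protocol does not say which. Having had no menstrual pain since treatment, she may well tick a relief answer, and three of the five answers count as success.

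At stake are the Month-1 relief rate, which Section 13.3.3 reports with a 95% confidence interval, and the Month-1 Dysmenorrhea and Menorrhagia Scores, which it tests by the signed-rank test. The Month-3 primary rate would be affected only if some women have no period for about eleven weeks or more. There is no control arm in which the same artefact would appear and cancel.

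**Working it through.** **Inputs from the protocol.** Visits at Months 1 and 3, each ±2 weeks (11.5). Null rate 0.777, expected rate 0.90, one-sided 0.025, 72 evaluable and 80 enrolled (11.4, 13.3.2).

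**Assumptions, not in the protocol.** A month is 30 days and three months 91 days, so Visit 3 falls on days 16–44 and Visit 4 on days 77–105. The procedure falls uniformly over a cycle of length L. A menses lasts 5 days.

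**The plan's own figures.** A one-sample z-test with null variance, its power found by binomial enumeration, gives 82.0% power at n = 72 (critical count 63), and 72/0.9 = 80. The sample size reproduces, and this point does not change it.

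**Month 1.** At day t:
- share with no onset = max(0, 1 − t/L)
- share without a completed menses = max(0, 1 − (t − 5)/L)

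On single days the no-onset share is:
- day 16: 1 − 16/28 = 43% for L = 28; 1 − 16/35 = 54% for L = 35
- day 30: 0% for L = 28; 1 − 30/35 = 14% for L = 35
- day 44: 0% for both

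Averaged over visits spread evenly on days 16–44 (a 28-day span):
- no onset, L = 28: (28 − 16)²/(2 × 28)/28 = 9%
- no onset, L = 35: (35 − 16)²/(2 × 35)/28 = 18%
- not completed, L = 28: (33 − 16)²/(2 × 28)/28 = 18%
- not completed, L = 35: (40 − 16)²/(2 × 35)/28 = 29%

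With visits clustered near day 30 instead (normal, assumed SD 5 days), the same shares are:

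| | L = 28 | L = 35 |
| --- | --- | --- |
| No onset | 4% | 15% |
| Not completed | 14% | 29% |

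**Month 3.** The same no-onset formula gives:

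| Cycle length | Day 77 | Day 91 |
| --- | --- | --- |
| up to 60 days | 0% | 0% |
| 90 days | 14% | 0% |
| 120 days | 36% | 24% |

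Only cycles longer than about 77 days, or amenorrhoea, expose the primary endpoint.

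**Effect on the primary decision, worst case.** With an exact interval the trial passes at 70 of 80 or 64 of 72. Suppose k women have no period and all are scored as successes, while the rest have a true rate of 0.777. The chance of passing is P(Bin(n − k, 0.777) ≥ pass mark − k):

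| k | n = 80 | n = 72 |
| --- | --- | --- |
| 0 | 1.9% | 1.2% |
| 2 | 2.5% | 1.6% |
| 4 | 3.2% | 2.1% |

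**The case against.** A reader might infer that the primary result is seriously biased, since one or two women can decide a threshold test. The documents do not support that. The Month-1 percentages do not carry over to Month 3, where women with cycles up to about 77 days have all had an onset. Eligibility requires a Dysmenorrhea Score of at least 4 and FSH below 40, which favours women with current menstrual pain. Hormonal contraception is ruled out. Estrogen, progesterone and oral contraceptives are prohibited during the trial apart from a one-time exception (11.6.3), which removes common drug causes of absent periods. Even in the worst case, two such women among 80 only bring the pass chance to the nominal 2.5%. That one woman can tip a result holds for any pass mark and does not show that such women exist.

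A reader might also infer that the error runs only toward success, or that a woman without a period is forced to choose an answer. The text shows neither. She could compare with her last period before the procedure and tick ineffective, or leave the item blank and be excluded under Section 13.2.3. A lean toward success is plausible, not proven.

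It is also fair that the Month-1 rate is secondary and decides nothing, that sites may book visits after a period, and that the questionnaire, which is not shown, might state a recall period.

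What stands is that the protocol, which defines the endpoint, leaves the rating untied to a menses. A later analysis convention cannot repair this unless menstrual dates or a no-menses answer have been collected.

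**Conclusion.** The point holds chiefly for the Month-1 secondary scores. Under assumed 28- to 35-day cycles, roughly 4–18% of women would rate before any post-procedure onset and 14–29% before completing a menses. The range reflects cycle length and how visits spread over the window, neither of which the protocol gives. Those ratings do not measure the device effect.

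For the primary endpoint the exposure is confined to very long cycles or amenorrhoea. It is possible because peri-menopausal women and women recently off hormone therapy are eligible, but it probably concerns few. The main loss there is that such women cannot be identified, so the effect can be neither bounded nor tested. This is a cheap improvement, not a flaw that undermines the trial.

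**What to change.** In Sections 11.5 and 12.2, tie each Relief, Dysmenorrhea and Menorrhagia rating to the most recent completed menses, which for Visits 3 and 4 must have followed the procedure. Record its start date on the existing questionnaire. Add an answer for no menses since the procedure and state that it never counts as relief.

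- **Month 1:** treat that answer as not evaluable and report how many women gave it.
- **Month 3:** keep these women in the FAS denominator as not improved for the primary analysis, with a sensitivity analysis that excludes them. State that the answer is a valid response and not a missing value. Otherwise Section 13.2.3 would drop treated women from the primary denominator for a post-treatment reason.

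The cost is one date and one answer box, with no extra visit and no change in sample size. A few Month-1 ratings become non-evaluable, and the Month-3 rate may be slightly less favourable.

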**11.5.1. Subject Number**

A management log will be created for all subjects who have signed the subject consent form and are enrolled for study participation. This management log is used to assign sequential subject numbers to subjects enrolled in the clinical trial, and a ‘Screening number’ and an ‘enrollment number’ will be assigned to subject numbers.

ALPINION Medical Systems Co., Ltd. 22/45

[figure not shown]

[figure not shown]

Protocol No. APM-03 Version 1.10/Date 20180103

[figure not shown]

The Screening number is assigned as a subject identification number according to the method below, by including one-digit institution number, ‘S’ for screening and a two-digit number assigned in the order of subject such as 01, 02, 03, and so on.

- One-digit clinical trial site number: Seoul National University Hospital –1, Konyang University Hospital -2

- Screening: S

- Two-digit number in the order of enrollment:

Example) The subject identification number for the first screened subject at the Seoul National University Hospital: 1 S – 0 1

The enrollment number is assigned as a subject identification number according to the method below, by including one-digit institution number and a two-digit number assigned in the order of subject such as 01, 02, 03, and so on.

- One-digit clinical trial site number: Seoul National University Hospital –1, Konyang University Hospital -2 - Two-digit number in the order of enrollment

Example) The subject identification number for the first enrolled subject at the Seoul National University Hospital: 1 – 0 1

**11.6. Clinical Trial Method**

**11.6.1. Instructions for Use for the Investigational Medical Device**

The procedure for using the investigational medical device is as follows, and for details of each subparagraph, follow the manufacturer’s instruction manual (attached).

Preparations Before Use

§ Check power and ON/OFF

§ Check image transducer connection and disconnection

§ Check whether image transducer is enabled or disabled

Instructions for Use and Operation Method

① Prepare device

② Prepare subject

1. Pre-procedure process
2. Outpatient treatment
   - Subjects who have received CT, MRI, or ultrasound images from the hospital where adenomyosis was first diagnosed, diagnostic images from the hospital currently providing treatment, or other treatment history or findings, etc. are treated. When a subject is identified as eligible for treatment, an appointment for the procedure is scheduled.
3. Preparation of the subject before the procedure (according to the surgeon's prescription)
   - Fasting the day before procedure
   - Keep clean skin
   - Hair removal depending on skin condition (mechanical and chemical hair removal)
   - Administer anesthetic or sedation according to the prescription of the procedure

ALPINION Medical Systems Co., Ltd. 23/45

[figure not shown]

[figure not shown]

Protocol No. APM-03 Version 1.10/Date 20180103

[figure not shown]

● Position : Supine or lateral

● Measurement of vital signs (blood pressure, pulse, respiration rate)

2. HIFU Procedure

1. After checking subject preparation for the procedure, the treatment area is scanned. The surgeon cauterizes the lesion tissue according to the pre-established procedure plan. The procedure usually causes tissue necrosis with a single procedure.
2. The surgeon checks the necrosis of the lesion in real time during the procedure through ultrasound and, if necessary, fixes the subject in place.

1. Post-procedure process
   1. Subjects who have completed treatment may return home on the day of treatment to engage in social activities or be hospitalized for about a day and return home the next day according to the opinion of the medical staff.
   2. Outpatient visit and follow-up tests: MRI is performed at 1 month and 3 months after the procedure to track the effect of the procedure and to measure the volume of the necrotic lesion tissue.
2. Precautions for Use

<See Attachments> ALPIUS 900 User Manual

